#### Follow up

2.4.5

After enrollment, all participants will undergo seven follow-up assessments. Outpatient visits will be scheduled at weeks 4, 8, and 12 post-treatment, with a ±3-day window from the start of medication administration. Additionally, outpatient or telephone follow-ups will occur at weeks 12, 24, and 36 after completion of the medication regimen.

### Outcome

2.5

The details of items to be measured and time points for data collection are shown in **Table 2**.

**Table 2 T2:** Trial schedule.

Study phase		Screening period	Intervention period (12 weeks)			Follow-up period (36 weeks)		
Visit		V1	V2	V3	V4	V5	V6	V7
		-3–0 days	Week 4 ± 3 days	Week 8 ± 3 days	Week 12 ± 3 days	Week 24 ± 3 days	Week 36 ± 3 days	Week 48 ± 3 days
Informed consent		**×**						
Random allocation		**×**						
Inclusion/Exclusion Criteria examination		**×**						
Baseline data collection	Demographic information	**×**						
	Medical history	**×**						
	Past medical history, allergies	**×**						
Safety evaluation	Vital signs	**×**	**×**	**×**	**×**	**×**	**×**	**×**
	Blood and urine routines	**×**			**×**			
	Liver and renal function	**×**			**×**			
	coagulation function	**×**			**×**			
	ECG	**×**			**×**			
	TnI or TnT	**×**						
Outcome evaluation	HAMD-17	**×**	**×**	**×**	**×**	**×**	**×**	**×**
	SAQ	**×**	**×**	**×**	**×**			**×**
	PHQ-9	**×**	**×**	**×**	**×**			**×**
	HAMA	**×**	**×**	**×**	**×**			**×**
	GAD-7	**×**	**×**	**×**	**×**			**×**
	DARS	**×**	**×**	**×**	**×**			**×**
	SF-36	**×**	**×**	**×**	**×**			**×**
	MoCA	**×**	**×**	**×**	**×**			**×**
	CEPT	**×**			**×**			
	IL-1β, IL-6, GDF15, and sCD40L	**×**			**×**			
	HPA	**×**			**×**			
	BDNF	**×**			**×**			
	MACCE		**×**	**×**	**×**	**×**	**×**	**×**
	AE		**×**	**×**	**×**			
Investigational Medication Distribution		**×**	**×**	**×**				
Investigational Medication Collection			**×**	**×**	**×**			
Log Cards Issuance		**×**	**×**	**×**				
Log Cards Collection			**×**	**×**	**×**			
Record drug combination		**×**	**×**	**×**	**×**	**×**	**×**	**×**
CRF principal investigator examination								**×**
CRF monitor examination								**×**

HAMA-17, Hamilton depression rating scale; MACCE, Major adverse cardiovascular and cerebrovascular events; SAQ, Seattle angina questionnaire; PHQ-9, Patient health questionnaire-9; HAMA, Hamilton Anxiety Scale; GAD-7, Generalized anxiety disorder-7; DARS, Dimensional Anhedonia Rating Scale; SF-36, Short form 36 health survey; MoCA, Montreal cognitive assessment; CPET, cardiopulmonary exercise testing; IL-1β, Interleukin 1 beta; IL-6, Interleukin 6; GDF15, Growth differentiation factor 15; sCD40L, Soluble CD40 ligand; CRF, Corticotropin-releasing factor; ACTH, Adrenocorticotropic hormone; BDNF, Brain-derived neurotrophic factor; TnI, Troponin I; TnT, Troponin T; ECG, Electrocardiogram; AE, Adverse event.

#### Patient characteristics

2.5.1

Demographic factors include age, gender, height, weight, ethnicity, educational level, socioeconomic status, and family history of hereditary diseases. Psychiatric history includes previous mental illness episodes and current or previous use of psychiatric medications. Lifestyle factors include smoking status, alcohol consumption, and physical activity levels. Cardiac history includes first occurrence status, ACS subtype, previous percutaneous coronary intervention (PCI) or coronary artery bypass grafting (CABG), myocardial injury biomarker abnormalities, and coronary artery condition. Comorbidities include hypertension, diabetes mellitus, hyperlipidemia, renal disease, hepatic disease, and other relevant conditions. This information will be collected at baseline and evaluated during the data management.

#### The primary and secondary outcomes

2.5.2

##### Primary outcome

2.5.2.1

The Hamilton Depression Rating Scale (HAMD-17) will be evaluated at each visit. The primary outcome is the proportion change in patients with a reduction rate more than 50% or a HAMD-17 score of less than 7 after 12 weeks of treatment. The reduction rate will be calculated using the following formula: [(baseline score - score at week 12)/baseline score] × 100%. The efficacy index is classified into three categories: cured (HAMD-17 score < 7), effective (reduction rate > 50%), and ineffective (reduction rate < 50%). The overall response rate is calculated as: [(cured cases + effective cases)/total cases] × 100%.

##### Secondary outcomes

2.5.2.2

The secondary outcomes are as follows:

Major Adverse Cardiovascular and Cerebrovascular Events (MACCE), defined as a composite of cardiovascular death, nonfatal myocardial infarction, revascularization, and stroke. These events will be recorded throughout the study period. The cumulative incidence of MACCE will be analyzed over the 36-week follow-up period.The Seattle Angina Questionnaire (SAQ) evaluates five health domains in patients with stable coronary artery disease: physical limitation, anginal stability, anginal frequency, treatment satisfaction, and disease perception.The Patient Health Questionnaire-9 (PHQ-9), Hamilton Anxiety Scale (HAMA), Generalized Anxiety Disorder-7 (GAD-7) and Dimensional Anhedonia Rating Scale (DARS) will be administered at baseline, and at weeks 4, 8, and 12 post-treatment, as well as at the 36-week follow-up, to assess anxiety and depressive symptoms.The Short Form-36 Health Survey (SF-36) will be administered at baseline, and at weeks 4, 8, and 12 post-treatment, as well as at the 36-week follow-up, to assess patients’ quality of life.The Montreal Cognitive Assessment (MoCA) will be administered at baseline, and at weeks 4, 8, and 12 post-treatment, as well as at the 36-week follow-up, to evaluate cognitive function.Improvement of Indicators in Cardiopulmonary Exercise Testing (CPET): (a) Metabolic Equivalents (METs), exercise time, Peak oxygen uptake (PeakVO2), oxygen pulse (VO2/HR), oxygen uptake relative to work rate (ΔVO2/ΔWR), and ventilatory anaerobic threshold (VAT). These parameters reflect exercise tolerance and cardiovascular function. (b) Breathing reserve (BR), the dead space volume/tidal volume ratio (VD/VT) and breathing frequency (Bf). These parameters reflect ventilatory function. (c) Partial Pressure of End-Tidal Carbon Dioxide (PETCO2), and the ventilatory equivalent of carbon dioxide (VE/VCO2 slope): These reflect the efficiency of pulmonary gas exchange. CPET includes over 50 indicators, each of which holds prognostic significance across cardiovascular conditions.Inflammatory cytokines (IL-1β, IL-6, GDF15, and sCD40L) and hormones related to the HPA axis—corticotropin-releasing factor (CRF), adrenocorticotropic hormone (ACTH), and cortisol—will be measured. BDNF will also be assessed. Blood samples will be collected before treatment and on the day of the end-of-treatment.

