#### Inclusion criteria

2.2.2

Patients who eligible for the trial must fulfill all of the following criteria at the time of randomization:

Participants are aged between 18 and 75 years.A confirmed diagnosis of ACS within 2 to 12 weeks prior to enrollment, with hemodynamic stability and absence of acute cardiovascular complications.Participants exhibited persistent symptoms of depressed mood or anhedonia for at least 2 weeks, with 17 < HAMD-17 ≤ 24All eligible participants must provide written informed consent.

Note:

Depressed Mood: The affective manifestation persists nearly daily for the majority of waking hours, manifesting through either subjective affective experience (e.g., persistent feelings of sadness, emotional emptiness, or hopelessness) or objective behavior observed by others (e.g., frequent episodes of tearfulness).Anhedonia: Present almost daily occurrence for most of the day. This involves a significant decrease in interest or pleasure in all or almost all activities (which can be either self-reported or observed).

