#### Adverse events

2.5.5

This study will monitor all adverse events (AEs), serious adverse events (SAEs), and adverse drug reactions (ADRs). All AEs must be promptly documented in both the source documents and the CRFs upon discovery. If an AE is classified as an SAE or a serious ADR, it must be reported in accordance with the applicable reporting procedures.

Due to the nature of the underlying diseases in this study, participants may experience clinical deterioration during the observation period, potentially requiring hospitalization or resulting in life-threatening events. However, MACCE is a predefined efficacy outcome in this study. Therefore, the occurrence of these events will not be documented as AEs. Likewise, hospitalizations or deaths resulting from these events will not be reported as SAEs.

All AEs must be followed until the participant’s condition returns to baseline (pre-treatment) levels or stabilizes. Investigators are responsible for continuous monitoring to ensure participant safety throughout the study.

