## Conclusion

4

This multicenter, randomized, double-blind, placebo-controlled clinical trial is designed to evaluate the efficacy of SGJY in treating depressive state after ACS, thereby providing a foundation for high-quality, evidence-based assessments of SGJY. The long-term follow-up component, which monitors MACCE, aims to provide evidence supporting the potential role of SGJY in improving long-term outcomes in patients with depressive state after ACS.

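### The MACCE composite counts any revascularization in patients enrolled 2 to 12 weeks after ACS, so a procedure scheduled before randomisation counts if it falls in the MACCE window, which is itself unclear

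*Protocol article*

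**What the plan says.** Section 2.5.2.2 of the protocol article lists MACCE first among the secondary outcomes, "defined as a composite of cardiovascular death, nonfatal myocardial infarction, revascularization, and stroke". Death is limited to cardiovascular death and infarction to nonfatal infarction; revascularization is not limited in any way.

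Two sentences on timing follow: "These events will be recorded throughout the study period" and "The cumulative incidence of MACCE will be analyzed over the 36-week follow-up period". Table 2 collects MACCE at V2 to V7 (weeks 4 to 48) and labels V5 to V7 (weeks 24, 36 and 48) as the 36-week follow-up period, after the 12 weeks of treatment. The Discussion also places the 36 weeks after treatment.

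On entry, section 2.2.2 requires "A confirmed diagnosis of ACS within 2 to 12 weeks prior to enrollment, with hemodynamic stability and absence of acute cardiovascular complications". The exclusion criteria (2.2.3) do not mention a pending procedure. The cardiac history taken at baseline (2.5.1) covers "previous percutaneous coronary intervention (PCI) or coronary artery bypass grafting (CABG"), but not procedures still to come.

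Section 2.5.5 states that "MACCE is a predefined efficacy outcome in this study" and on that ground keeps these events out of adverse event reporting. The Conclusion says that the long-term follow-up "aims to provide evidence supporting the potential role of SGJY in improving long-term outcomes".

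**The concern.** In the weeks after ACS, a second procedure may already be on the calendar at enrolment. That decision precedes study drug, so the procedure says nothing about whether the drug alters the course of disease. Under the definition as printed it is still a MACCE if it falls in the counted window.

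Such events should occur equally often in both arms under double-blind 1:1 randomisation. They favour neither arm. They raise the reported event rate, move a ratio measure towards 1 and lower power. The Conclusion gives the MACCE comparison some weight, and the Discussion already concedes a risk of a false negative, which it attributes to short follow-up. Counting planned procedures would be a second source, and an avoidable one. Unless planned status is captured at baseline, separating these procedures reliably at the end will be harder.

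**Working it through.** **1. What could remove a planned procedure.** The MACCE definition (2.5.2.2), the exclusion criteria (2.2.3), the baseline data (2.5.1) and Table 2 contain no exclusion, baseline field or counting rule for a procedure scheduled before randomisation.

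**2. Which procedures fall in the window.** Entry is 2 to 12 weeks after ACS and treatment lasts 12 weeks.
- Counting from randomisation (weeks 0 to 48): procedures from 2 to 12 weeks after ACS onward count.
- Counting over the post-treatment 36 weeks only: 2 + 12 = 14 and 12 + 12 = 24, so only procedures done at least 14 to 24 weeks after ACS count. Earlier ones are recorded but not analysed.

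**3. The plan's own figures.** The article gives no MACCE rate, effect or power to reproduce. Its sample size rests on HAMD-17 response (45.7% against 69%) and is not affected by this point.

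**4. Illustrative MACCE risks, counting from randomisation.** The Introduction cites a 32.5% risk of recurrent coronary events within 2 years after discharge, and a 51% increase in major cardiovascular events with depression in coronary disease. Assume that these apply to this trial's MACCE, that the hazard is constant, and that an effective drug removes all of the excess linked to depression.
- Cumulative hazard over 48 weeks without the excess: −ln(1 − 0.325) × 48/104 = 0.1814, a risk of 1 − exp(−0.1814) = 16.6%. This is taken as the active-arm risk.
- Control: 0.1814 × 1.51 = 0.2739, a risk of 1 − exp(−0.2739) = 24.0%.
- Hazard ratio: 1/1.51 = 0.66. Risk difference: 7.4 points.

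**5. Adding planned procedures.** Let a share s of each arm have a counted planned procedure, independent of true events. The share is not in the article; 5, 10 and 15% are assumptions.
- Observed risk in an arm with true risk p: s + (1 − s)p.
- Observed hazard ratio: ln(1 − active risk) / ln(1 − control risk).
- Observed risk difference: (1 − s) × 7.37 points.
- Expected events: 74 × (control risk + active risk). Power is for a two-sided 5% test of two proportions with 74 per arm.

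| s | Control risk | Active risk | Hazard ratio | Risk difference (points) | Events | Power |
|---|---|---|---|---|---|---|
| 0 | 24.0% | 16.6% | 0.66 | 7.4 | 30 | 20% |
| 5% | 27.8% | 20.8% | 0.72 | 7.0 | 36 | 17% |
| 10% | 31.6% | 24.9% | 0.76 | 6.6 | 42 | 14% |
| 15% | 35.4% | 29.1% | 0.79 | 6.3 | 48 | 13% |

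**6. Sensitivity to the assumed rates.** With a true control risk of 12%, a true risk ratio of 0.50 and s = 10%, the control risk is 0.10 + 0.90 × 0.12 = 20.8% and the active risk 0.10 + 0.90 × 0.06 = 15.4%. The ratio becomes 0.74, power falls from 25% to 13%, and the risk difference goes from 6.0 to 5.4 points. At the same s, a true ratio of 0.50 becomes 0.79 when the control risk is 8% and 0.71 when it is 16%. The direction is always the same; the size depends on the assumptions.

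**The case against.** The strongest objection is the analysis window. Read literally, the article analyses MACCE only over the 36 weeks after treatment. A reader might infer from the definition alone that staged procedures soon after ACS will enter the comparison and that the 48-week figures above describe what will happen. The article does not support that: on the literal reading, procedures in the 12 treatment weeks are recorded but not analysed, and those are where early staged procedures would fall. This objection stands and limits the point. It does not remove it, because neither window excludes a planned procedure that falls inside it, and the article's recording and analysis sentences give different periods.

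Second, a journal article condenses the full protocol, and finer event definitions may sit there. That is fair for adjudication and diagnostic thresholds. Here, however, the composite is stated component by component, with two components qualified and this one not, so the point concerns what the printed definition counts.

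Third, the size is hypothetical. That stands: the share of planned procedures is assumed, and the 24% risk and hazard ratio of 0.66 follow from the Introduction only under the assumptions listed. The ratio is also the measure that moves most. The article specifies cumulative incidence and names no hazard ratio for MACCE, and the risk difference shrinks only by the factor 1 − s.

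Fourth, an unqualified component is simple and objective, whereas planned status needs a judgement. A V1 record made before allocation is known keeps that judgement small.

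Last, a reader might infer bias towards one arm. Double-blind 1:1 allocation gives no ground for that.

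**Conclusion.** The point holds as a minor, inexpensive improvement. As printed, the definition counts any revascularization in the MACCE window, including one scheduled before randomisation, and nothing else in the article prevents this. The effect is non-differential dilution of the ratio, not bias towards an arm.

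The magnitude is not established. The 0.72 to 0.79 range applies only if counting starts at randomisation and if 5 to 15% of patients have such a procedure. Under the literal 36-week post-treatment window the dilution is probably small, provided most staged procedures are done within a few months of ACS, on which the article is silent. MACCE is secondary, does not set the sample size, and has only about 20% power on the illustrative rates even with no planned procedures counted. It would be too strong to say that the dilution decides the MACCE result.

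**What to change.** - In 2.5.2.2, define the component as revascularization not planned before randomisation.
- Add one V1 case report form field for any coronary procedure already scheduled, completed before allocation. Leave such a procedure out of MACCE unless it is brought forward by a new ischaemic event.
- List all revascularizations, planned and unplanned, in a descriptive table by arm.
- Reconcile the recording and analysis sentences so that one MACCE window is stated, with its start and end.

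If the full protocol already does this, the article needs only to say so. The cost is a short change of wording, one baseline field, a simple planned/unplanned classification and one table, with slightly fewer counted events. Sample size and visits do not change.

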### Design and settings

2.1

This is a multicenter, randomized, double-blind, placebo-controlled clinical trial. The trial was registered on the National Medical Research Registration and Filing Information System (www.medicalresearch.org.cn) on June 19, 2024 (Registration No. MR-11-24-037476), and on the International Traditional Medicine Clinical Trial Registry (itmctr.ccebtcm.org.cn) on June 1, 2024 (Registration No. ITMCTR2024000099). All documents, including the study protocol, informed consent forms, and case report forms (CRFs), comply with the Declaration of Helsinki and have been reviewed and approved by the Xiyuan Hospital Ethics Committee of the Chinese Academy of Medical Sciences (approval number: 2024XLA062-3). The clinical trial protocol follows the SPIRIT 2025 statement (14). The trial will be conducted in accordance with the Good Clinical Practice (GCP) Guidelines (2020) and reported according to the CONSORT 2025 statement (15).

Patients will be recruited from five centers in China: Xiyuan Hospital, China-Japan Friendship Hospital, the Eighth Affiliated Hospital of Sun Yat-sen University, the Third People’s Hospital of Fujian Province and Xuzhou City Hospital of TCM. A total of 148 participants will be enrolled after providing written informed consent. Participants will be randomly assigned in a 1:1 ratio to receive either SGJY or placebo, with a 12-week treatment period followed by a 36-week follow-up. A schematic diagram of the study procedures is presented in **Figure 1**.

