#### Termination and dropout of trial patients

2.2.4

Patients who fail to meet the inclusion criteria or fulfill any exclusion criteria.Patients with poor protocol compliance or who withdrew prematurely from the trial.Patients with incomplete medical records that hinder the evaluation of efficacy and safety.Patients whose condition deteriorated rapidly during the study, including those with acute cardiovascular events or malignant neoplasms.Patients whose depression worsens during the trial (HAMD-17 score >24 for over two weeks) or who display suicidal ideation.Patients with serious adverse events during the trial.Voluntary withdrawal by the patient.

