This study aims to assess the efficacy of SGJY in treating depressive state after ACS by examining series of clinical scales, inflammatory cytokines, and related proteins (IL-1β, IL-6, GDF15, and sCD40L). In addition, a 36-week follow-up will be conducted after SGJY treatment to record the incidence of MACCE and evaluate long-term prognosis. Clinical studies have shown that improvements in cardiac and pulmonary function reduce ischemic burden in patients with coronary artery disease (35), and that exercise capacity is a strong predictor of adverse cardiovascular events (36). Therefore, CPET will be included in the trial to assess patients’ cardiopulmonary endurance. Additionally, the study will measure serum levels of HPA axis-related hormones (CRF, ACTH, and cortisol) and BDNF. Upon activation of the HPA axis, the paraventricular nucleus of the hypothalamus synthesizes and releases more CRF. The CRF is transported to the anterior pituitary, where it stimulates the secretion of ACTH into the systemic circulation. ACTH acts on the zona fasciculata of the adrenal cortex promoting the synthesis and release of cortisol. HPA axis dysfunction and subsequent elevation of cortisol levels contribute to the progression of depression and an increased risk of adverse cardiovascular events (22). BDNF is a biological marker associated with depression and CHD. Reduced BDNF level is associated with an increased risk of depression in patients with ACS. Moreover, Meta-analyses have demonstrated an increase in BDNF after antidepressant treatment (37). Metabolomic analyses will be conducted to investigate the potential mechanisms through which SGJY exerts its antidepressant effects in patients with depression after ACS. GDF15 is a stress-responsive inflammatory cytokine primarily secreted by activated macrophages. Elevated GDF15 levels are closely associated with cardiovascular disease severity, increased risk of adverse cardiovascular events, and the presence of depressive symptoms (38–41). sCD40L serves as a diagnostic biomarker for atherosclerosis, a condition strongly associated with cardiovascular mortality and non-fatal myocardial infarction (42, 43). Serum sCD40L levels are also significantly elevated in individuals with depression, further increasing their risk of cardiovascular disease (44, 45).Therefore, GDF15 and sCD40L may serve as surrogate endpoints for predicting adverse cardiovascular events and may also reflect the severity of depressive symptoms.

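### MACCE are recorded from the first weeks on drug, but the stated analysis window starts after treatment ends, so on-treatment events enter no stated comparison between arms

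*Protocol article*

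**What the plan says.** All references are to the protocol article.

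- **Recording.** On MACCE, section 2.5.2.2 (Secondary outcomes) says: "These events will be recorded throughout the study period". Table 2 (section 2.5) agrees, with MACCE ticked at V2 to V7, weeks 4 to 48.
- **Analysis.** The next sentence of section 2.5.2.2 reads: "The cumulative incidence of MACCE will be analyzed over the 36-week follow-up period".
- **Meaning of the period.** Section 2.1 describes the design "with a 12-week treatment period followed by a 36-week follow-up", and the Abstract gives the same order. Table 2 has separate column groups for the intervention period (V2 to V4) and the follow-up period (V5 to V7, weeks 24, 36 and 48). The Discussion (section 3) says "a 36-week follow-up will be conducted after SGJY treatment to record the incidence of MACCE".
- **Safety reporting.** Section 2.5.5 says that, because MACCE is a predefined efficacy outcome, "the occurrence of these events will not be documented as AEs". Hospitalisations and deaths resulting from them are likewise not reported as SAEs.
- **Termination.** Section 2.2.4 lists under termination and dropout: "Patients whose condition deteriorated rapidly during the study, including those with acute cardiovascular events or malignant neoplasms".
- **Analysis sets.** Section 2.7 applies intention to treat to efficacy. The FAS is all randomised patients less severe inclusion violators and those never treated.

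**The concern.** Recording and analysis cover different spans. The events left over are those that occur while patients take SGJY or placebo, when a pharmacological effect in either direction is most directly expected.

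The safety rule makes this more serious. MACCE are taken out of AE and SAE reporting because the efficacy analysis is meant to cover them, yet the stated efficacy window does not reach the treatment weeks. An infarction or cardiovascular death at week 6 would be recorded as a MACCE but would appear in no comparison of arms that the article describes.

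MACCE is the first-listed secondary outcome, and the Conclusion (section 4) presents it as the trial's evidence on long-term outcome.

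**Working it through.** **Plan's own figures.** The article gives no expected MACCE rate or power, so there is nothing to reproduce for this outcome. The sample size (67 per group, section 2.3.3) reproduces with the unpooled two-proportion formula for 45.7% against 69%, but it concerns HAMD-17 response and has no bearing here.

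**Step 1: the window.**

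| | Weeks from start of treatment | Source |
|---|---|---|
| MACCE recorded | 0–48 (visits at weeks 4 to 48) | 2.5.2.2, Table 2 |
| MACCE analysed, as written | 12–48 | 2.5.2.2, with 2.1, Table 2 and Discussion |
| On drug | 0–12 | 2.1, 2.4.2 |

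Omitted: 12/48 = 25% of observation time, and 12/12 = 100% of time on drug. This step needs no assumption.

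**Step 2: share of first events outside the window (illustration).** The only background rate in the article is 32.5% recurrent coronary events within 2 years (Introduction). Assume that it applies to MACCE at a constant hazard over 104 weeks.

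- Hazard λ = −ln(1 − 0.325)/104 = 0.00378 per week.
- Risk by week 12 = 1 − exp(−12λ) = 4.43%; × 148 = 6.6 patients.
- Risk by week 48 = 1 − exp(−48λ) = 16.59%; × 148 = 24.6 patients.
- Share in weeks 0–12 = 4.43/16.59 = 27%; about 18.0 first events remain in the window.

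Sensitivity to the assumptions:

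| Hazard in weeks 0–12 relative to later | Share outside window, Introduction rate | Share outside window, assumed 48-week risk 5% to 20% |
|---|---|---|
| 1× | 27% | 25% to 27% |
| 2× | 43% | 41% to 43% |
| 3× | 53% | 51% to 53% |

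The multipliers are assumptions with no source in the article.

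**Step 3: what an effect confined to the drug period would look like.** Take the same λ, 74 per arm, and an assumed hazard ratio of 0.5 or 2 during weeks 0–12 only.

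| On-drug HR | First events weeks 0–12, SGJY vs placebo | First events weeks 0–48, SGJY vs placebo |
|---|---|---|
| 0.5 | 1.7 vs 3.3 | 10.9 vs 12.3 |
| 2 | 6.4 vs 3.3 | 15.0 vs 12.3 |

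The article does not name the MACCE denominator, so both candidates are worked:

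- *Patients event-free and in study at week 12.* The 36-week risk is 1 − exp(−36λ) = 12.7% in both arms, and the effect disappears. This set is selected after randomisation and conflicts with the intention-to-treat principle in section 2.7.
- *The whole FAS.* The arms stay as randomised, but only first events in weeks 12–48 count. For HR 2 that is 15.0 − 6.4 = 8.6 on SGJY against 12.3 − 3.3 = 9.0 on placebo. For HR 0.5 it is 10.9 − 1.7 = 9.2 against 9.0. The on-drug difference is again absent.

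Under either denominator the window hides an on-treatment effect.

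**The case against.** **Loose wording.** Section 2.5.2.2 also uses the 36-week follow-up as the name of a visit (V7, week 48) for PHQ-9, SF-36 and MoCA, and the sentence just before the analysis sentence covers the whole study. The authors may have meant cumulative incidence up to that last visit. That is possible, but the article nowhere says it. The MACCE sentence names a period, and the other sections place that period after treatment. This stands as a reason to treat the point as an inconsistency to correct, not as a proven intention to discard on-drug events.

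**Randomisation.** A reader might infer that the arms compared are no longer the randomised ones, because section 2.2.4 terminates patients with acute cardiovascular events. The documents do not support that as a fact. No section sets a week-12 risk set, and section 2.7 states intention to treat on the FAS. Section 2.2.5 asks for continued contact and feasible assessments after dropout, and section 2.8 asks for follow-up to the end of the study. Post-randomisation selection is a consequence of one possible denominator only.

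**Choice of test.** A reader might also infer that only chi-squared or Fisher's test is planned and that censoring is ignored. Section 2.7 also names the CMH test with site stratification, and logistic regression. Time-to-event and competing-risk methods are details that an article commonly leaves to the SAP.

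**Importance.** MACCE is secondary, the trial is sized on HAMD-17, and the Discussion already concedes a false-negative risk for MACCE. At an assumed HR of 0.7, power is about 11% with 18 events and 14% with 24, so neither window gives a sensitive test. This stands and limits what the correction buys inferentially. It does not answer the reporting gap, since on-drug events should be shown by arm whatever the power.

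**Conclusion.** The point holds for the window. As written, the MACCE analysis covers weeks 12–48, and MACCE in the 12 treatment weeks enter neither a stated between-arm efficacy comparison nor AE and SAE reporting. The firm size is 25% of observation time and all time on drug. The 27% of first events is an illustration. It borrows a two-year rate for recurrent coronary events, which is neither this composite (which includes stroke) nor this population (enrolled 2 to 12 weeks after ACS, with advanced heart failure excluded), and it assumes a constant hazard. The event counts should not be read as forecasts. Loss of the randomised comparison is conditional on a denominator that the article does not state. The HAMD-17 primary analysis is untouched.

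**What to change.** 1. In section 2.5.2.2, replace the analysis sentence with wording such as: the outcome is the first MACCE from randomisation to week 48, in the full analysis set, compared between arms with stratification by centre.
2. Present weeks 0–12 and 12–48 separately by arm as description only.
3. Reconcile sections 2.2.4, 2.5.2.2 and 2.5.5, so that a patient with an early event stays in MACCE ascertainment whatever happens to treatment, and on-treatment MACCE are reported by arm. Whether treatment stops is a clinical matter on which this point takes no position.
4. Leave the time-to-event or competing-risk model to the SAP.

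The cost is a few sentences. Table 2 already collects MACCE at V2 to V7, and section 2.2.5 already asks for contact after dropout. The change should be made before unblinding.
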